## Abstract

**Background:**

The transition between acute care and community care represents a vulnerable period in health care delivery. The vulnerability of this period has been attributed to changes to patients’ medication regimens during hospitalization, failure to reconcile discrepancies between admission and discharge and the burdening of patients/families to take over care responsibilities at discharge and to relay important information to the primary care physician. Electronic communication platforms can provide an immediate link between acute care and community care physicians (and other community providers), designed to ensure consistent information transfer. This study examines whether a transfer-of-care (TOC) communication tool is efficacious and cost-effective for reducing hospital readmission, adverse events and adverse drug events as well as reducing death.

**Methods:**

A randomized controlled trial conducted on the Medical Teaching Unit of a Canadian tertiary care centre will evaluate the efficacy and cost-effectiveness of a TOC communication tool. Medical in-patients admitted to the unit will be considered for this study. Data will be collected upon admission, and a total of 1400 patients will be randomized. The control group’s acute care stay will be summarized using a traditional dictated summary, while the intervention group will have a summary generated using the TOC communication tool. The primary outcome will be a composite, at 3 months, of death or readmission to any Alberta acute-care hospital. Secondary outcomes will be the occurrence of post-discharge adverse events and adverse drug events at 1 month post discharge. Patients with adverse outcomes will have their cases reviewed by two Royal College certified internists or College-certified family physicians, blinded to patients’ group assignments, to determine the type, severity, preventability and ameliorability of all detected adverse outcomes. An accompanying economic evaluation will assess the cost per life saved, cost per readmission avoided and cost per QALY gained with the TOC communication tool compared to traditional dictation summaries.

**Discussion:**

This paper outlines the study protocol for a randomized controlled trial evaluating an electronic transfer-of-care communication tool, with sufficient statistical power to assess the impact of the tool on the significant outcomes of post-discharge death or readmission. The study findings will inform health systems around the world on the potential benefits of such tools, and the value for money associated with their widespread implementation.

**Trial registration:**

ClinicalTrials.gov NCT01402609.

## Background

The transition between acute care and community care represents one of the most vulnerable periods in health care delivery, particularly as the complexity of inpatient populations increases. The vulnerability of this period has been attributed to three main factors. First, changes to patients’ medication regimens during hospitalization are numerous, yet failure to reconcile discrepancies between admission and discharge is frequent [1]. Second, the patient/family is required to take over care responsibilities at discharge and must often personally relay important information to the primary care physician
[1]. This can be particularly challenging if the TOC information is poorly communicated, presented too rapidly, if instructions are verbal only, or if the patient struggles with health literacy
[1-3]. Finally, crucial information is often not transferred between acute care physicians and community physicians [1].

Information about the hospitalization (such as medication changes, patient diagnoses, interventions, diagnostic findings, and necessary follow-up) is commonly transferred to the community care physician through a summary of the patient’s acute care stay that is faxed or mailed. Deficits with respect to timeliness and/or complete failure to transmit are widespread
[1,4]. At the first post-discharge appointment, this summary is unavailable to the community care physicians up to 75% of the time
[1,5-7]. This negatively impacts the continuity of care provided to many patients
[1,7]. When summaries are received, inconsistent content and inaccuracies are common
[1,4]. Acute care physicians, whether medical or surgical, often neglect to include diagnostic findings, treatment/hospital course, discharge medications, pending tests results, and whether the patient and family received counseling
[7].

Computer-enabled TOC communications have potential to avert such problems. These communication tools, operating on electronic health record or web-based platforms can provide an immediate link between acute care and primary care physicians, and interfaces can be designed to ensure consistent information transfer. In addition, physicians in both settings have expressed preference for electronic discharge documents over hand written/dictated summaries with respect to clarity, comprehensiveness, and positive impacts on continuity of care
[8-11].

Kripalani and collegues
[4] published a systematic review examining the prevalence of discharge communication deficits and looked broadly at all types of interventions that target those deficits. Very few of the interventions reviewed by Kripilani et al. involved significant contributions from electronic medical record data to construct the discharge summary, and none used the internet to transmit information. However, the publications years considered spanned 1977 to 2005.

In recent years, original studies
[9-20] have emerged assessing the efficacy of computer enabled TOC communication compared to traditional summaries. In the context of a rapidly growing literature on electronic medical records and telehealth interventions, our team systematically reviewed the literature and identified 12 controlled studies assessing the efficacy of computer-enabled TOC communication tools
[14]. The findings in the literature globally indicate that compared to traditional TOC summaries, computer-enabled TOC communications of various types appear promising, particularly with respect to improving timeliness of discharge summary delivery, and satisfaction among physicians and patients/families. There are also some positive impacts on overall patient management and continuity of care. However, only four of these studies reported the effects of such tools on the notable clinical endpoints of hospital readmission, post-discharge mortality, and adverse events
[14], and in doing so, none had sufficient statistical power to assess these endpoints. As a result, only one study
[15] in our review demonstrated a reduction in readmission to hospital within 12 months due to the implementation of a web-based TOC communication platform. Our published systematic review identified a need for a well-designed, sufficiently powered study evaluating relevant clinical outcomes associated with an electronically based TOC tool. Given the growing demand and monetary investments associated with these tools, such a study would have implications on a global scale.

The Ward of the 21^st^ century (W21C) initiative at the University of Calgary, in Alberta, Canada is an interdisciplinary research and innovation program focused on health system safety and quality (see
http://www.w21c.org). The W21C team, working collaboratively with Alberta Health Services, the provincial health authority, undertook iterative consultation with multiple clinical stakeholders as well as patients and family, and developed an electronic communication TOC tool. The tool was built off of the already functioning electronic platform called Sunrise Clinical Manager (SCM) that physicians use to manage inpatient orders and to access patient medical records, diagnostic imaging and laboratory results. An initial pilot test of the tool involving 100 actual patient transfers of care summaries from an adult internal medicine ward to the community was performed on the Medical Teaching Unit (MTU) affiliated with the W21C. This pilot study involved detailed assessments of usability issues, provider and patient satisfaction, completeness and timeliness of the discharge summaries. The information generated from this pilot led to the refinement of the tool to the extent that it satisfied the needs of acute care physicians, primary care physicians, and patients. The refined tool will be made available for use by physicians and medical students on the MTU and used for this study.

On this backdrop of iterative tool development and pilot work, a protocol for a randomized controlled trial to more definitely test the efficacy of the TOC communication tool was developed. With funding from the Canadian Institutes of Health Research, the RCT will assess the efficacy of the TOC communication tool for reducing the endpoint of death or hospital readmission at 3 months. Secondary objectives are: i) to assess the impact of the tool on the occurrence of post-discharge adverse events and adverse drug events; ii) to evaluate the cost-effectiveness of the tool.

## Methods

### Setting

The study will be conducted on the Medical Teaching Unit (MTU) of a Canadian tertiary Medical Center. The MTU is a general internal medicine unit that provides care to adults who have non-surgical medical problems that necessitate hospitalization. The typical patient on the team has multi-system disease and/or complex symptom presentations that require detailed diagnostic evaluation and/or inpatient therapies. Patients typically have multiple comorbid illnesses and complicated medication profiles that require careful scrutiny and review at time of discharge. Pilot work on the MTU revealed that approximately one in four patients discharged from the unit were readmitted within a 3 month period (i.e., 51 out of 219 cases reviewed in our pilot work).

The MTU consists of three physician teams working in parallel on multiple hospital wards throughout the hospital. The three teams have indistinguishable clinical expertise and consist of similarly-trained attending staff physicians and rotating medical residents and students. They care for similar patient populations and work in the same environment, with assistance from the shared nurse discharge coordinator. The teams are already undertaking a diligent process of pre-acute care discharge preparation (i.e., prior to implementation of the TOC communication tool) in which attempts are made to prepare communication materials for community providers. This is therefore a highly appropriate setting for the study of a TOC tool, because the patient population is at high risk for readmission, and one for whom enhanced clinical communication produced by the TOC communication tool can be evaluated on a backdrop of already diligent discharge preparation practices.

### Participants

All patients admitted to the MTU will be considered for this study. Patients will be excluded if the patient and/or family member declines consent; is under 18 years of age; cannot provide contact information; and/or family member lacks English proficiency and the team cannot communicate with them; has a research burden (enrolled in 2 other studies); is admitted under or has their acute care transferred to a clinical service other than the MTU; is not an Alberta resident; was previously enrolled in the study; is being discharged to hospice care; is transferred to another Hospital (“Rapid Transport”); is incoherent; or dies in hospital.

Written information about the study will be provided to patients before obtaining informed consent. The study has been approved by the Conjoint Health Research Ethics Board at the University of Calgary (# 23469) and registered at ClinicalTrials.gov (NCT01402609).

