**Figure 3 F3:**
[figure not shown]
Existing health issues off of a test patient from the seamless transfer-of-care tool.

Upon admission to the MTU, the research team will approach the patient for consent and will collect baseline data including socio-demographic information, co-morbidities (using the Charlson co-morbidity measurement method
[21]), and current health status using the Health Utilities Index (HUI)
[22,23]. A chart review will be conducted on each patient. This information will be collected on a secure, web-based program that was developed by the University of Calgary’s new Clinical Trial Research Unit (CRU). The CRU has also generated a web-based method for random allocation of patients to intervention *versus* control. Randomization will be requested from the investigators, and will be entirely concealed from the researchers. Randomization will be performed within 48 hours of patients leaving hospital rather than at the time of them leaving due to the nature of the MTU in which, decisions about when patients can leave often occur without much notice and residents often do not have time to complete a summary immediately given competing clinical activities. To ensure that patients will be leaving the hospital with either a copy of the completed summary produced by the TOC tool or, conversely, a hand written note for the control group, the summaries will be started by providers some time prior to the patient leaving. Figure
4 provides a summary of this process.

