### Outcome measures

The primary outcome of interest for the clinical trial is the composite, at 3 months, of death or readmission to any Alberta acute-care hospital. Secondary outcomes of interest are the occurrence of post-discharge adverse events and adverse drug events at 1 month post discharge. Patient health status, meanwhile, will be assessed at baseline, 1 and 3 months using the Health Utilities Index
[22,23].

The elements of our composite primary outcome (i.e., death or readmission) are identified for study because these are recognized to be major events that we are ultimately trying to prevent through safer health care. The 3 month time frame is felt to be most relevant, because it is short enough to potentially relate to discharge communications, but also long enough after discharge to permit some events to accrue. The primary outcomes of interest will be assessed through existing linkages to hospitalization data from the Alberta Health Services Health Outcomes Group (for readmission to acute care hospitals), and to the Alberta Vital Statistics for post-discharge mortality. Such an approach to post-discharge outcome ascertainment avoids the shortcoming of unreliable patient self-report on readmission, and the potential challenges associated with determining vital status of patients that we are unable to reach by telephone.

The outcomes of post-discharge adverse events and adverse drug events will be determined using the method described by Forster and colleagues
[24,25]. At 1 month post discharge, a trained investigator, blinded to patient group assignments, will administer a telephone survey using a survey tool that takes approximately 15 minutes to complete to determine the post-hospital course for all consenting patients. This will allow us to determine readmission/physician visits/emergency department visits, and whether an adverse event or adverse drug event occurred. Two Royal College certified internists or College-certified family physicians, also blinded to patients’ group assignments, will independently rate the type, severity, preventability and ameliorability of all possible adverse events. Adverse events will be classified into the following types: 1. adverse drug events; 2. procedure-related injury; 3. nosocomial infection, 4. care-related fall, 5. therapeutic error, 6. diagnostic error or 7. other types. Further information on this validated multi-step method is available elsewhere
[24,25].

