### Data analysis

The baseline characteristics (age, sex, principal diagnosis categories, and comorbididy conditions) of intervention and control subjects will be recorded and compared between groups using Chi-square tests or Fisher Exact tests where appropriate. We will also use t-tests for comparison of continuous variables. The same statistical tests will be used to compare outcomes between the two groups. Chi-square and Fisher exact tests will be used to compare the frequency of dichotomous outcomes (i.e., death or readmission, adverse events, adverse drug events). For the subset of patients who are readmitted in the two groups, we will use t-tests to compare the time-to-readmission of patients and patient health status (HUI3 overall scores) in the intervention *versus* control groups. A Kaplan-Meier analysis with log-rank test will be used to perform a time-to-event analysis in all subjects. For the economic evaluation, total costs of care and outcome events will be calculated for each arm of the trial. For each outcome, the cost difference between arms will be divided by the benefit difference to result in cost to benefit ratio.

The analysis will be performed by intention-to-treat. Patients will be analyzed in the group to which they were randomized, even if the summary of their hospital stay is generated using a communication method that differs from their group assignment. CONSORT reporting guidelines (
http://www.consort-statement.org) will be used to diligently track and report treatment crossovers and losses to follow-up through a progressive flow-chart. We will work diligently during the course of the study to limit the frequency of such occurrences. This will be achieved by a system of clear labeling of patient charts immediately after random allocation so that the care team will be aware of the assigned summary of care communication method. Research associates affiliated with the study will also be present among the clinical care team daily to reinforce the issue of compliance to patient assignments.

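### The exclusions for in-hospital death, hospice discharge and transfer have no cut-off at randomization, so applying them as written could drop randomized patients on events related to the primary outcome

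*Protocol article*

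**What the plan says.** The Participants section gives one undivided list of exclusions. Beside criteria known at admission (age, residency, consent), it names events that occur during or at the end of the stay. A patient is excluded who "is admitted under or has their acute care transferred to a clinical service other than the MTU", who "was previously enrolled in the study; is being discharged to hospice care; is transferred to another Hospital", or who "is incoherent; or dies in hospital". No point in time is given after which these stop applying.

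Under Study design, consent and baseline data are obtained on admission, but allocation comes later: "Randomization will be performed within 48 hours of patients leaving hospital rather than at the time of them leaving". The reason given is that "decisions about when patients can leave often occur without much notice".

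Under Data analysis, adherence to the assigned method is supported by "clear labeling of patient charts immediately after random allocation so that the care team will be aware" of the assigned method. The same section declares an intention-to-treat analysis. It spells this out for one situation only, a summary produced by a method other than the one assigned.

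Under Outcome measures, the primary outcome is "the composite, at 3 months, of death or readmission to any Alberta acute-care hospital". Deaths come from a linkage to provincial vital statistics, described there as a source for mortality after discharge.

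**The concern.** Allocation precedes departure by up to two days, and departure is hard to predict. A patient can therefore be randomized and then die, be moved to another service or hospital, or be sent to hospice. Read literally, the list excludes that patient even though the allocation has been made and is visible on the chart.

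Two things are at stake. First, the primary denominator would no longer be all randomized patients. Second, the grounds for removal are not neutral. In-hospital death is the same kind of event as one component of the composite, and discharge to hospice or transfer plausibly marks patients at higher risk. If such removals differed between arms, the comparison would shift, and a larger sample would not correct it. Concealment of the allocation sequence does not help, because it protects only up to the moment of allocation.

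**Working it through.** **Inputs from the protocol article (Sample size calculation):** control rate 0.25, intervention rate 0.1875, difference 0.0625, two-sided alpha 0.05, power 0.80 (printed there as beta), 686 per group required, 700 per group planned.

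**Inputs assumed, because the article gives none:** x, the fraction of one arm removed in excess of the other; and r, the 3-month event risk of those removed.

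**1. The plan's own figure.** Pooled-variance formula without continuity correction, mean rate 0.21875:

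n = [1.960 × √(2 × 0.21875 × 0.78125) + 0.8416 × √(0.25 × 0.75 + 0.1875 × 0.8125)]² / 0.0625² = 685.6, rounded up to 686. The stated figure is reproduced. Power is 80.0% at 686 and 80.8% at 700 per group.

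**2. Equal removal from both arms.** The cost is precision only, and it is small:

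| Removed from each arm | Left per group | Power |
|---|---|---|
| 1% | 693 | 80.4% |
| 2% | 686 | 80.0% |
| 5% | 665 | 78.8% |

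**3. Excess removal from one arm.** The rate observed in that arm becomes (0.25 − x·r)/(1 − x), so it falls by x(r − 0.25)/(1 − x).

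| r | x = 1% | x = 2% |
|---|---|---|
| 40% | 0.01 × 0.15/0.99 = 0.15 points | 0.02 × 0.15/0.98 = 0.31 points |
| 80% | 0.01 × 0.55/0.99 = 0.56 points | 0.02 × 0.55/0.98 = 1.12 points |
| 100% | 0.01 × 0.75/0.99 = 0.76 points | 0.02 × 0.75/0.98 = 1.53 points |

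Against the 6.25-point target, the 1% column runs from 0.15/6.25 = 2% to 0.76/6.25 = 12%, and the 2% column from 0.31/6.25 = 5% to 1.53/6.25 = 24%.

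**4. Extreme case for the type I error.** Suppose there is no true effect (25% in both arms), patients are removed from one arm only, and all of them would have had the event. With 1% removed (7 of 700), the two-sided rejection probability is 6.2%; with 2% (14 of 700) it is 10.2%. This is an upper bound for those fractions, not a forecast.

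**5. Cost of keeping everyone.** If 2% of intervention patients never receive the assigned summary and carry the control risk, the intervention rate is 0.98 × 0.1875 + 0.02 × 0.25 = 0.18875. The difference is 0.25 − 0.18875 = 6.1 points, and power at 700 per group is 79.1% against 80.8%.

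**The case against.** The list has an ordinary reading in which nothing goes wrong. Patients consent on admission and are randomized only near departure, so death, transfer and hospice planning between those two points are exactly what an eligibility list would need to cover. The article condenses a fuller protocol, and Figure 4, which summarizes the process, is not in the text available for this review; it may show where exclusions fall. The intention-to-treat statement can be read as governing every patient once randomized. The arms differ only in how the summary is produced, and no mechanism is documented by which that would change who dies or is transferred in the last 48 hours. Death also leaves little room for discretion.

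Much of this stands. A reader might infer that the care team, knowing the arm, decides who is excluded. No text says so: the team is told the arm so that it uses the assigned method. A reader might also infer that the list flatly contradicts intention-to-treat. It does not: an eligibility list without a time stamp is unreconciled with that statement, not opposed to it. The express conflict in the article is a different one: the Discussion expects a patient whose assigned method is not followed to be excluded, against the Data analysis section.

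What remains is that neither reading is fixed by the text. The intention-to-treat explanation covers only a change of summary method, and the Discussion shows that removal after randomization was contemplated in at least one situation.

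**Conclusion.** The point holds as a gap in the wording with a possible, unquantified bias. Applied as written, the exclusions could remove randomized patients, with the arm known, on events related to the primary composite, and the article does not say how this fits its intention-to-treat rule. It does not show that such removals will happen, who would make them, or that they would differ between arms.

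The effect is probably small. Per excess percentage point removed from one arm, the shift is about 0.15 to 0.76 points for an assumed event risk of 40% to 100%. Both the excess and the risk are assumptions with no source in the document. Equal removal costs almost nothing in power. A claim that the trial's result would be materially biased is therefore not supported. The case for acting is that the gap can be closed at very little cost.

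**What to change.** State in Participants that in-hospital death, hospice discharge, and transfer to another service or hospital exclude a patient only up to randomization, and re-check these criteria when the web allocation is requested. Then:

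- Keep every randomized patient in the primary analysis, in the assigned arm.
- Count any death after randomization as a primary event, including one before leaving hospital.
- Follow hospice discharges and transfers through the existing provincial linkage, with an explicit rule that a direct inter-hospital transfer is not itself a readmission.
- Report these cases by arm in the CONSORT flow chart.
- Align the Participants, Data analysis and Discussion sections on what happens to a patient after randomization.

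The cost is a short wording amendment and one check on the randomization screen. There are two downsides. Some patients will never receive the assigned summary, which dilutes the effect slightly (power about 79% instead of 81% if this is 2% of the intervention arm). And an endpoint framed as post-discharge is widened slightly to take in the few deaths between randomization and discharge; the outcome definition should say so.
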